## Abstract

**Methods::**

This study will be a randomized controlled clinical trial. A triage of individuals between 4 and 17 years old with a diagnosis of sleep bruxism will be carried out at the clinic of the Catholic University of Uruguay, and in a private office referred by different private care centers. The selected participants will be evaluated before and after treatment by means of questionnaires on bruxism, sleep quality and nocturnal oxygen saturation measurement. For this, 46 patients with sleep bruxism will be recruited, who will be divided into 2 groups: control group (CG), which will undergo an application of placebo ILIB and an orofacial myofunctional therapy (MFT) exercise protocol; and na ILIB group, which will carry out an active application of ILIB and an exercise protocol, this being once a week for 8 weeks. The laser treatment (808 nm) will be performed twice a week for 8 weeks. The values will be tested for normality by the Kolmogorov–Smirnov test. For the comparison between the groups, *t* test will be carried out, considering a level of significance of 0.5% (*P* < .05).

**Discussion::**

Although local photobiomodulation (PBM), acupuncture PBM and physiotherapy have been studied in the treatment of bruxism, this is the first study to evaluate the effect of ILIB combined with myofunctional exercises for sleep bruxism in pediatrics.

## 1. Introduction

Bruxism is a repetitive activity that involves clenching or grinding the teeth during sleep or wakefulness.^[1,2]^ In 2013, in an international consensus, it was defined as “a repetitive masticatory muscular activity, with clenching or grinding of the teeth and/or by the fixation (bracing) or thrust (thrusting) of the jaw.” In 2018, a new update was made, in which the thrust and fixation mandibular movements are defined in detail.^[3]^ The grinding is generally audible and triggers discomfort or side effects for those who present it. This condition is commonly seen in children and adolescents.^[4]^ If it is not identified and addressed in time, it can bring negative consequences such as tooth wear, periodontal disease, hypertrophy of the masticatory muscles, headache, limitation of mouth opening, muscle pain and temporomandibular disorders (TMD) and, in many cases, decrease in academic performance of the child or adolescent.^[5]^

Regarding the etiology of bruxism, there is consensus in the literature that bruxism has a multifactorial etiology.^[6]^ The genetic causes related to a possible polymorphism, anxiety, some personality traits, and endocrine alterations associated with stress, among others, are considered. It has also been related to occlusal factors, malocclusion, nutritional deficiencies, respiratory problems (apneas, snoring), allergies, intestinal parasites, oral habits, changes in neurotransmitters such as dopamine and sleep quality.^[7]^

When it comes to the diagnosis of bruxism, there are controversies. Currently, it is considered that only polysomnography can give a definitive diagnosis, but this exam has a high cost.^[8]^ Polysomnography allows simultaneous monitoring of electroencephalographic, electrocardiographic, electromyographic sleep, and respiratory signals during sleep.^[9]^ Self-questionnaires are usually used (in the case of pediatrics it is completed by the parents or the referent), based on the criteria of the American Association of Sleep Medicine. The prevalence is highly controversial. In the analysis of systematic reviews, a prevalence of 22% to 31% for sleep bruxism in adults was shown.^[10]^

Regarding therapeutics, they are mostly palliative, addressing the symptom, but without providing a solution. A systematic review suggests that the evidence is still scarce in relation to drugs.^[11]^ Botulinum toxin protects orofacial structures (teeth, jaw muscles, temporomandibular joint) reducing the damage caused by bruxism, generating a decrease in pain and symptoms related to excessive muscle contraction.^[12]^ Occlusal devices, such as splints, are used to protect teeth from the damage caused by clenching and grinding during bruxism.^[13]^ Photobiomodulation (PBM) is a very promising, painless and low-cost option; capable of stimulating or inhibiting cellular processes.^[14]^ Intravascular Irradiation of Blood (ILIB), a systemic modality of PBM, can be used as a complementary therapy to other therapies.^[15]^ It emits energy that activates neurohumoral regulation and synchronization and cell modulation with antioxidant, metabolic, immunological, antispasmodic, sedative, healing, analgesic, anti-inflammatory and blood circulation-increasing effects.^[16,17]^ Orofacial myofunctional therapy (MFT) is a set of techniques and procedures whose objective is to promote changes in muscle patterns and orofacial functions through isotonic and isometric exercises with the orofacial and oropharyngeal muscles supported by the functions of breathing, chewing, swallowing and talk.^[18]^ Orofacial MFT and systemic low intensity laser administration are options to more traditional therapies.

The objective of this study is to determine the efficacy of ILIB in sleep bruxism, in combination with oral MFT. It also aims to evaluate the relationship between oxygenation and bruxism during sleep and to determine the prevalence of nocturnal hypoxemia and its association with daytime oral breathing.

## 2. Methods/design

### 2.1. Study design

This is the first version of a study protocol for a randomized, controlled, parallel group, single blind, clinical trial, with a control group (CG) and na active comparator group, in which 46 individuals with a diagnosis of sleep bruxism will participate. The project was evaluated and approved by the Research Ethics Committee of *Universidad Católica del Uruguay* (process number 220211) and was registered in the Clinical Trials platform (https://clinicaltrials.gov/) with the number NCT05301452, first published on March 16, 2022 and last updated on August 4, 2022. Recruitment and treatments will be performed at the dentistry clinic of Universidad Católica del Uruguay clinics, during the period from September 1, 2022 to December 1, 2022.

This protocol is in accordance with the 2013 SPIRIT (Standard Protocol Items: Recommendations for Interventional Trials) Statement. The SPIRIT checklist can be found as an additional file and Figure 1 is the SPIRIT figure.

**Figure 1. F1:**
[figure not shown]
SPIRIT figure as recommended by 2013 SPIRIT statement. SPIRIT = standard protocol items: recommendations for interventional trials.

### 2.2. Participants

A triage of individuals between 4 and 17 years old, diagnosed with sleep bruxism, will be carried out at the dentistry clinic of the Catholic University of Uruguay. Patients will already be in treatment for other conditions at the clinic, what will facilitate recruitment. It is believed that the need for treatment of bruxism before major pain symptoms or dental wear will help to improve adherence to the trial.

Inclusion criteria:

Children in the mixed dentition phase (permanent incisors and first molars erupted);Or adolescents with an established permanent dentition.

Exclusion criteria:

People with dental caries;Those taking medications, such as inflammatory agents, muscle relaxants, corticosteroids, anticonvulsants, and antidepressants;Those with chronic diseases that affect muscles or motor coordination, and those who do not cooperate during the evaluation will be excluded from the study;Children with cerebral palsy;Patients whose guardians do not sign the informed consent or the participant who does not sign the assent form.

### 2.3. Experimental groups

Forty-six patients with sleep bruxism will be recruited and divided into 2 groups:

- CG which will undergo an application of placebo ILIB and an orofacial MFT exercise protocol;

- ILIB group, which will carry out an active application of ILIB and an orofacial MFT exercise protocol, this being once a week for 4 weeks.

### 2.4. Sample calculation

The sample was calculated to detect a significant difference between PBM and MFT with 80% power and a significance level of 5%, considering the oxygen saturation index. Based on the study by Aarab et al^[19]^ to detect a difference in saturation index, with an effect size of 0.53, the minimum number per group should be 23 participants per group (Fig. 2).

**Figure 2. F2:**
[figure not shown]
Sample size calculation. Analysis: A priori: Compute required sample size; Input: Tail(s) = One; Effect size dz = 0.5373031; *α* err prob = 0.05; Power (1-*β* err prob) = 0.8; Output: Noncentrality parameter *δ* = 2.576815; Critical t = 1.7171444; Df = 22; Total sample size = 23; Actual power = 0.8027361.^[19]^

### 2.5. Randomization

To randomly distribute the individuals in the experimental groups, a random sequence generator (https://www.randomizer.org/tutorial/) will be used. Opaque envelopes will be identified with each number and inside it a sheet containing the information of the corresponding experimental group will be inserted. The envelopes will be sealed and kept in a safe place until the time of the procedures. The generation of the sequence and the preparation of the envelopes will be performed by a person who is not involved in the study.

### 2.6. Blinding

The participants will not know whether they belong to the placebo/CG, or the active PBM group, seeing as the laser application will be simulated. Unblinding is not permissible.

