### 2.7. Interventions

#### 2.7.1. ILIB protocol.

The laser treatment will be performed by a speech therapist, using the wavelength of 660 nm. It will be done once a week for 4 weeks, in 20-minute sessions. In the CG, the ILIB procedure will be simulated, but with the laser turned off.

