#### 2.7.2. Orofacial MFT.

MFT will be performed by a speech therapist specialized in the area. It will consist of 1 weekly session, where the functions of breathing, chewing and swallowing will be evaluated and addressed.

The following exercises will be indicated: nasal hygiene, inflated cheeks with the tip of the tongue on the palate, lingual sweep, tongue thrust against the palate, tongue touch on the last molars, chewing of soft solids and bolus assembly (20 minutes therapy session).

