### 3.2. Breathing

A clinical evaluation will be carried out by a speech therapist specialized in the area of Orofacial Motricity, to check for possible improvement in breathing. It is the respiratory characterization from the taking of air, which explains the anatomical and topographical situation of its entrance to the respiratory system (respiratory mode), to the thoracoabdominal movement zone that integrates inspiration and expiration. It is supported by the observation with the aid of a Glatzel’s mirror to anatomically determine the upper airway status and its functional correlation.

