### 3.6. Presence of bruxism

The bruxism questionnaire will be delivered to parents or guardians, which will be completed prior to treatment and afterwards. The questionnaire contains 4 questions regarding the perceived presence of bruxism, and 5 questions for the dentist to answer, based on a clinical observation. All questions have the options “yes” or “no.” The more times the word “yes” is chosen, the greater the risk for bruxism is.

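### Only participants are masked: no masked assessor is named for the five secondary outcomes that clinicians rate, and the laser-off sham depends on an inconsistently stated wavelength

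*Protocol article*

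**What the plan says.** Section 2.1 of the protocol article describes a "randomized, controlled, parallel group, single blind, clinical trial". Section 2.6 says who is masked: "The participants will not know whether they belong to the placebo/CG, or the active PBM group, seeing as the laser application will be simulated". No other role is named there.

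On delivery, section 2.7.1 states: "The laser treatment will be performed by a speech therapist, using the wavelength of 660 nm". For the sham it adds: "In the CG, the ILIB procedure will be simulated, but with the laser turned off". The abstract gives another wavelength: "The laser treatment (808 nm) will be performed twice a week for 8 weeks". Section 2.7.2 assigns the exercises, which both arms receive, to the same profession: "MFT will be performed by a speech therapist specialized in the area".

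On assessment, section 3.2 states: "A clinical evaluation will be carried out by a speech therapist specialized in the area of Orofacial Motricity, to check for possible improvement in breathing". Sections 3.3 to 3.5 use the same arrangement for swallowing, chewing and speech. Section 3.6 splits the bruxism questionnaire into 4 items for parents and "5 questions for the dentist to answer, based on a clinical observation". Section 3.7 has parents complete 44 sleep items. Section 3.1 makes recorded nocturnal oximetry the primary outcome.

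**The concern.** The single-blind label and section 2.6 together fix masking at the participant. This is a stated design choice, not a detail that a short article happens to omit: a fuller document that masked the assessors would contradict the label.

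The person running the laser cannot be masked. That person is a speech therapist, and a speech therapist also scores four outcomes, with nothing in the article to keep the two tasks apart. A dentist, whose knowledge of allocation is not addressed, answers more than half of the bruxism items. A rater who knows the arm and is looking for improvement can shift yes/no answers and clinical judgements towards the active laser.

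This matters although the primary outcome comes from a device. The stated objective in the introduction is the efficacy of the laser in sleep bruxism, and the questionnaire in 3.6 is the only outcome that measures bruxism directly. The result closest to that objective therefore rests on human ratings.

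Participant masking in turn rests entirely on the simulated application. If children or parents could tell that the laser is off, the parent-completed bruxism and sleep items would be exposed as well.

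**Working it through.** The plan gives no figure on this point to reproduce. The check is a count of outcomes by who produces the value.

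| Section | Outcome | Source of the value | Masked assessor named? |
|---|---|---|---|
| 3.1 | Oximetry (primary) | Recording device | Reader not mentioned |
| 3.2 | Breathing | Speech therapist, with Glatzel mirror | No |
| 3.3 | Swallowing | Speech therapist, with Payne's test | No |
| 3.4 | Chewing | Speech therapist, gnathodynamometer reading | No |
| 3.5 | Speech | Speech therapist, with Glatzel test | No |
| 3.6 | Bruxism | Parents 4 items, dentist 5 items | No |
| 3.7 | Sleep quality | Parents, 44 items | Parents not named in 2.6 |

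**Counts**
- Assessed by a speech therapist: 4/7 = 57%.
- Assessed wholly or partly by a clinician: (4 + 1)/7 = 5/7 = 71%.
- Dentist's share of the bruxism items: 5/(4 + 5) = 5/9 = 56%.
- Clinician-assessed outcomes with a named masked assessor: 0 of 5.

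**Who must know the arm.** Section 2.7.1 has the laser on in one arm and off in the other, so its operator knows the allocation. For the therapist delivering the exercises, the assessing therapist and the dentist, the article states neither that they know nor that they do not.

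**The sham.** Light at 660 nm is visible red; light at 808 nm is near-infrared and practically invisible. If section 2.7.1 is right, an off laser could differ visibly from an active one wherever the emission point can be seen. If the abstract is right, the light itself would hardly give the arm away. The article does not describe shielding, eyewear, or the imitation of indicator lights or sounds.

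**What a given bias would do (illustration only).** The documents give no bias size, so I assume a range. Let knowledge of the arm shift a roughly continuous score by b standard deviations with no true effect. Take 23 per arm and the two-sided 5% t test, with 2 × 23 − 2 = 44 degrees of freedom and noncentrality b × √(23/2) = 3.39b. The chance of a significant result, nominally 5%, becomes:

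| Assumed b | Chance of P < .05 |
|---|---|
| 0.1 | 6.3% |
| 0.2 | 10.2% |
| 0.3 | 16.9% |
| 0.5 | 38.2% |

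These values show how sensitive the test is. They do not estimate what would happen in this trial.

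**The case against.** Three stronger readings are tempting, and the article supports none of them.

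- **That the assessors are unmasked, or that one therapist both treats and scores.** A reader might infer this from the single-blind label and the shared job title. The article does not say that the assessing therapist is the laser operator, and it gives the dentist no part in the laser sessions. Staff tasks may be set out in a fuller protocol. The exact statement is that nobody who rates is declared masked.
- **That the sham can be recognised by eye.** This needs visible emission, and the document gives two wavelengths. The groups are parallel, so each child sees one condition and may not know what an active session looks like. Nothing says that parents attend. Recognition is possible but not established.
- **That the whole trial rests on subjective ratings.** The primary outcome is recorded by a device, and rater bias does not act on it directly. Chewing is a force reading, so it depends on the operator but is not simply an opinion.

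It is also fair to object that separating the treating and scoring therapists is cheap only if two are already involved. If there is one, a second trained therapist would have to be found.

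All of this stands, and it limits the point. It does not remove it: on the plan's own terms masking stops at the participant, the laser operator knows the arm, and five clinician-assessed outcomes have no named masked rater.

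**Conclusion.** The concern holds in a limited form. The design as stated masks participants only. It names no masked assessor for 5 of 7 outcomes, all of them secondary. One of the five is the only direct measure of bruxism, with 5 of its 9 items answered by a dentist. Assessment bias is a real risk for these outcomes, less so for chewing. Its size cannot be derived from the article. The device-recorded primary outcome is not directly exposed.

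The weakness of the sham is conditional: it depends on which wavelength applies and on whether the emission or the device panel can be seen.

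The conclusion assumes that the single-blind label and section 2.6 describe the conduct of the trial. If a fuller protocol already masks the assessors, the label and section 2.6 are wrong and need correcting instead. The change should be made, but the primary analysis does not stand or fall by it.

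**What to change.** In section 2.6, state that:

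- only the laser operator opens the envelope and knows the allocation;
- the dentist, and whoever reads out the oximetry, are masked and absent from laser sessions;
- where more than one speech therapist is already involved, the one who scores outcomes 3.2 to 3.5 is masked and is not the laser operator; where only one is involved, these four outcomes are reported as unmasked assessments;
- the emission and the device panel are concealed in the same way in both arms.

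Then change the blinding label in 2.1 to match the roles actually masked. Reconcile the wavelength in 2.7.1 with that in the abstract; which one is correct is for the investigators to settle.

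The cost is small. Sealed envelopes prepared by someone outside the study already exist (2.5), withholding the allocation from the dentist needs no new staff, and concealment needs only a simple cover. The downside is less flexible scheduling. No second therapist is required, because the fallback is to report those outcomes as unmasked assessments.

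### The ban on unblinding in section 2.6 is stated without an exception for the safety of an individual child

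*Protocol article*

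**What the plan says.** Section 2.1 describes a "randomized, controlled, parallel group, single blind, clinical trial". Section 2.6 names only one masked party: "The participants will not know whether they belong to the placebo/CG, or the active PBM group, seeing as the laser application will be simulated". The next sentence is the whole of the unblinding rule: "Unblinding is not permissible". It carries no condition and names nobody who may make an exception.

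Three other places bear on it. Section 2.7.1 has a speech therapist deliver the laser and describes the sham: "In the CG, the ILIB procedure will be simulated, but with the laser turned off". Section 2.5 covers custody of the allocation: "The envelopes will be sealed and kept in a safe place until the time of the procedures". It adds that someone outside the study generates the sequence and prepares the envelopes, but does not say that this person keeps a list afterwards. Section 2.2 gives the population: "A triage of individuals between 4 and 17 years old, diagnosed with sleep bruxism".

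**The concern.** The article is not silent on unblinding. It fixes a rule, and the rule is absolute. A fuller protocol that allowed disclosure for safety would contradict this sentence rather than fill a gap in it, so the point cannot be set aside as detail that an article leaves out.

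The participants are minors, and the Introduction presents the intervention as a systemic form of photobiomodulation with, among others, sedative, immunological and circulatory effects. If a child had an unexpected event, the guardian or a treating clinician could reasonably ask whether the laser had been active. Under the sentence as written, a member of the study team who answered the guardian would breach the protocol. At stake is the interest of an individual child, not the trial's result.

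**Working it through.** The point turns on wording. The only arithmetic concerns the size of a single disclosure.

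**1. Is there an exception elsewhere?** The article was read from the abstract to the discussion for a code-break procedure, a safety condition or a person authorised to reveal allocation. There is none. The sentence in section 2.6 stands alone.

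**2. Whom does the rule bind?** Sections 2.1 and 2.6 together describe a single-blind trial with participants as the masked party. The sentence follows directly on the one about participants, so its natural subject is telling participants their group. For children aged 4 to 17 that includes the guardian. Extending it to an outside clinician is arguable, because no section describes such a person as masked.

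**3. Does the information exist in the team?** The sham is the same procedure with the device off (section 2.7.1), so the therapist who runs it very likely knows the arm. The article does not say so; this is an inference. If it is right, no code has to be broken, and what is missing is permission to pass the information on.

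**4. What does the ban protect?** The questionnaire in section 3.6 goes to parents or guardians and has 4 items on perceived bruxism, with 5 further items for the dentist. Section 3.7 gives parents or guardians a 44-item sleep questionnaire. Both are repeated after treatment. Parents or guardians are also trained for the oximetry (section 3.1). Family masking therefore has real value for the subjective outcomes.

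**5. What would one exception cost the comparison?**
- Inputs: 46 participants (section 2.3), 23 per group (section 2.4).
- Share of the sample: 1/46 = 0.022, about 2%.
- Share of one arm: 1/23 = 0.043, about 4%.
- If knowing the arm shifted that child's outcome by an amount *d*, the arm mean would move by *d*/23. Even with *d* equal to one standard deviation (an assumption chosen to be large), the mean moves by 0.043 standard deviations.
- The primary outcome is recorded oximetry (section 3.1), an instrument measure less open to family expectation than a questionnaire, so a shift of that size is unlikely there.
- Number of disclosures: the documents give no adverse-event rate. Assuming 0 to 1 in the trial, the affected share is 0% to 2.2%.

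**The case against.** The strongest reply is that the sentence concerns participants only, in a trial where the operator already knows the arm, and was meant to stop casual disclosure to families who fill in subjective questionnaires. Much of that stands. The ban has a scientific purpose and should be kept as the general rule. The practical consequence is also smaller than in a double-blind drug trial.

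It can also be said that the safety cost is not demonstrated. The article calls photobiomodulation painless and noninvasive and names no reaction in which knowing the arm would change care. That stands as a limit on severity. It does not justify an unconditional rule, since those descriptions do not exclude an unexpected event.

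What does not stand is that the operator's knowledge settles the matter: knowing the arm is not permission to disclose it.

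Two stronger readings are tempting and are not supported:
- A reader might infer that there is no route at all by which a clinician could learn the allocation. The text does not go that far, because only participants are described as masked and the information very likely sits with the operator.
- A reader might set the rule against the statement "This protocol is in accordance with the 2013 SPIRIT" and infer non-compliance. The checklist is an additional file that is not shown, and the article does not say what that standard asks for on unblinding. No such claim is made here.

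Finally, who discloses, from which source and how it is logged are details an article may leave to the full protocol. Only the unqualified ban is criticised.

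**Conclusion.** The point holds in a limited form. Section 2.6 states a ban that is reasonable as a general rule but lacks an exception for an individual child's safety. Read literally, it bars disclosure to the guardian and arguably to an outside clinician.

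The expected effect on the results is negligible: about 2% of the sample for one disclosure, provided the child stays in the analysis as randomised. The verdict rests on two assumptions that the documents do not confirm: that the operator knows the arm, and that a need to disclose would be rare (0 to 1 of 46). If need were more frequent, the exception would matter more for the children, and the loss of family masking would grow in proportion. Severity is low; this is a cheap improvement.

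**What to change.** Replace the sentence in section 2.6 with:

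> Unblinding is not permitted, except that an individual participant's allocation may be disclosed when the responsible clinician judges it necessary for that child's safety; each disclosure is documented and reported by arm, and the child remains in the analysis as randomised.

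The sponsor should name the source of the allocation, for example the treating operator's record. The replacement should not assume a list kept by the person who prepared the envelopes, because section 2.5 does not say that one exists. The clinical criteria for disclosure stay with the investigator.

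The cost is one sentence and a log entry for each disclosure. The downside is a rare loss of masking for a single family, which would bear mainly on that family's questionnaire answers.
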